### Statistics

#### Sample size calculation

Statistical analysis of the published clinical evidence regarding the fibrin sealant QUIXIL, demonstrating its effects in controlling haemostasis and reducing postoperative blood loss after TKR, was used as a basis to calculate the number of patients needed for this RCT. Based on the literature [7], a sample size estimation for changes in Hb level was made with the statistical program nQuery Advisor 5.

The estimation assumes the following mean values and standard deviations (SD) of postoperative decreases in Hb [7]: 25 g/l (SD 10) (study group) and 37 g/l (SD 12) (control group). The level of significance is set at *P* = 0.05 and a two-sided *t*-test is performed with equal numbers from the two groups. With a power of 90 % and an estimated SD of 15 g/l, the required number of cases is 34 per group. For this sample size estimation we assumed that the use of additional information such as baseline Hb levels as covariates would increase the power of the test.

For a total sample size of 68, approximately 120 patients must be screened because about 40 % of the eligible patients are expected either not to meet the inclusion criteria or not to consent to participate, owing to inconvenience with the follow-up examinations; not being randomised due to intraoperative circumstances; or to drop out for other reasons. Since the primary endpoint is blood loss during the first 7 days, which is calculated using routine blood tests during the inpatient stay, no drop-outs regarding the primary endpoint should be expected after surgery (Fig. 1).

**Fig 1 Fig1:**
[figure not shown]
Flow diagram of study participants. The CONSORT flow diagram shows the anticipated number of patients from enrolment until analysis

#### Statistical methods

The statistical analysis will be carried out at the end of the study; interim analyses are not intended. However, the analysis of the primary endpoint may be carried out earlier, as soon as the data from the last patient have been assessed. For this analysis, ANCOVA for Hb level differences baseline with respect to the detected minimum in the first 7 postoperative days for both treatment groups with adjustment for baseline Hb levels will be used. If the upper limit of the two-sided 95 % confidence interval (CI) of the difference in means between EVICEL™ and standard orthopaedic surgery as estimated from the ANCOVA model is <0, the superiority of EVICEL™ will be concluded. Missing values for Hb observations will be replaced by the last observation carried forward method (LOCF). If there are no postoperative Hb values available for a particular patient, that patient will be recorded as having the largest decrease in Hb of the control group.

AEs and SAEs will be evaluated descriptively by chi-squared tests.

For the secondary endpoints, the need for at least one transfusion will be analysed by odds ratios (OR) together with 95 % CIs. The ROM and the length of hospital stay will be analysed by *t*-tests. The total cost per patient will be analysed using Wilcoxon’s signed ranks test. Time until wound healing will be tested by log rank tests.

Secondary and tertiary analyses are exploratory and will be performed descriptively.

The *P* values will be assessed descriptively and will be deemed significant when *P* <0.05.

The primary analysis will be conducted on the intention to treat (ITT) population, that is, for all randomised patients. Sensitivity analyses will be performed in the per-protocol (PP) population, including all patients who completed the study according to the protocol.

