### Primary and secondary study endpoints

The primary endpoint of this study is postoperative blood loss after TKR, measured by the difference in Hb levels at baseline (recorded in the 3 days prior to randomisation) with respect to the detected minimum in the first 7 days postoperatively and compared between the study group and the control group. During this period, blood samples will be taken regularly according to the in-house protocol, and results will be compared with control values derived from patients treated under the same conditions but without the use of EVICEL™. During the operation, all factors that affect the postoperative level of Hb will be documented.

Secondary endpoints are the need for at least one allogeneic blood transfusion or one autologous transfusion, the ROM of the operated joint, the postoperative use of analgesics, time until wound healing, clinical outcome scores, length of hospital stay, and the overall cost of the treatment.

A follow-up measurement of ROM will be conducted 3, 6 and 12 months after surgery. The ROM of the operated joint in the study and the control group will be measured using the angle of maximum flexion. Factors that might influence the ROM (for example, the use of a peripheral nerve block) will be documented and might lead to exclusion from the secondary endpoint calculation (for example, preoperative maximal flexion <90°). The need for at least one blood transfusion will be compared between the study and the control group to demonstrate whether or not EVICEL™ reduces the need for transfusions. Furthermore, it should be shown that the use of analgesics (according to the WHO pain ladder [4]) can be reduced by treatment with EVICEL™ and that the time until the wound is completely dry is shorter. In addition, it should be shown that the clinical outcome in the EVICEL™ group is better than that in the control group. Clinical outcome is assessed by two different clinical outcome scores, the clinician-completed Knee Society Score (KSS) and the patient-completed Knee Injury and Osteoarthritis Outcome Score (KOOS) [5, 6].

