#### Preoperative examinations (baseline)

The preoperative examinations to establish baseline measures will include the following:Orthopaedic examination of the lower extremity, including measurement of ROM, and confirmation of the medical indication.Blood samples taken and tested according to in-house protocol. Relevant parameters for the study are: INR, PTT and complete blood count (CBC) without differential, including Hb and leucocytes. The amount of blood needed for this routine procedure is about 26.5 ml.Subcutaneous injection of certoparin-sodium (for example, Mono Embolex™) at a dose of 3,000 IU/day performed from the preoperative evening onwards. An equivalent drug might be used as an alternative, depending on the guidelines (for example, no preoperative administration in the case of some oral products).

The following general data will be collected on the corresponding case report form (CRF): patient ID; gender and date of birth; height and weight; BMI; medical history, especially regarding thromboembolic events; smoking status; comorbidities and concomitant medications. In addition, the following specific data will be assessed: indication(s) for TKR, Hb level (g/dl), C-reactive protein (CRP) (mg/dl), leucocytes (1/μl), virology (hepatitis B/C and HIV screening), haemostatic parameters (INR and PTT), ROM (angle of maximum flexion), details of medications used as prophylaxis against thrombosis, and assessment of KSS and KOOS.

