#### Postoperative procedure

The postoperative procedure is described as follows:Prophylaxis against thrombosis is continued with certoparin-sodium 3,000 IU (or alternative) once daily until the patient reaches a physiological level of activity.The bandages are removed on day 1 after surgery. Physiological exercises, manual lymphatic drainage and mobilisation of the patient under full weight-bearing begin on day 1, according to the established in-house standard. Sutures are removed between days 10 and 14.The standard postoperative transfusion criterion at the site is an Hb level <6 g/dl, or in case of values between 6 and 8 g/dl, more than mild symptoms of anaemia. However, the criteria are soft and must be adapted according to the patient’s individual situation and his/her comorbidities, especially any cardiac comorbidities. The decision for or against a transfusion is therefore made by the treating anaesthetist or orthopaedic surgeon, according to their clinical experience. Thus, the unlikely possibility of transfusing patients with Hb levels between 8 and 10 g/dl cannot be completely ruled out. For each transfusion performed, the reasons will be documented precisely.Collection of blood parameters, their analysis and the documentation of the secondary endpoints are carried out as described in point 6 (Assessment of Efficacy). The amount of blood taken for each of the four blood tests is about 8.2 ml.

The following postoperative data are collected in the corresponding CRF (parameters marked with an asterisk are also assessed during the follow-up examinations):Blood parameters: Hb level 7 days postoperatively, CRP, leucocytesIn case of blood transfusions: number of units transfused, date of transfusion, Hb value before transfusion, reason for transfusionROM: angle of maximum flexion*Use of analgesics (WHO pain ladder)*Time when nerve block catheter is removed (if appropriate)Complications (for example, disorders of wound healing, thromboembolic events, signs of infection, for example, abnormal redness, swelling, pain, loss of function, hyperthermia)*Time when the wound is completely dry and any kind of secretion has ceasedDuration of hospital stayKSS and KOOS assessments* Type of rehabilitation after hospital stay (stationary, ambulant or other)* Number of physiotherapy treatment units after rehabilitation, including manual lymphatic drainage* Total costs of TKR Theoretical date of discharge (defined in section ‘Primary and Secondary Study Endpoints’)

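### The primary ANCOVA adjusts for baseline Hb only; prespecifying blood volume, from sex, height and weight already recorded, could add some precision at almost no cost

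*Protocol article*

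**What the plan says.** Primary and secondary study endpoints defines the primary endpoint as "postoperative blood loss after TKR, measured by the difference in Hb levels at baseline", taken to the lowest value in the first 7 postoperative days. Statistical methods analyses this fall by ANCOVA "for both treatment groups with adjustment for baseline Hb levels will be used". No other covariate is named.

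Two other sections bear on the choice of covariates. Preoperative examinations (baseline) puts "gender and date of birth; height and weight; BMI" on the case report form. Sample size calculation states the expectation that "the use of additional information such as baseline Hb levels as covariates would increase the power of the test", without giving a size for the gain. The endpoint section adds: "During the operation, all factors that affect the postoperative level of Hb will be documented".

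Blood volume is not mentioned in the article. Trial status says that recruitment has not started.

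**The concern.** The quantity of interest is volume of blood lost; the quantity analysed is a change in concentration. The two are linked through blood volume, which differs between men and women and with body size. The inclusion criteria admit both sexes, and the exclusion criteria cap BMI only above 35, so blood volume will vary among the patients. If blood loss is not itself proportional to blood volume, part of the spread in Hb fall is predictable before surgery from variables the trial already holds. Leaving them out keeps that part in the error term, which widens the confidence interval and lets a chance imbalance in sex or body size add noise to the estimate.

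Precision would matter more if the planning difference proved optimistic. That difference comes from QUIXIL, whose fibrinogen component contains tranexamic acid, while that of EVICEL does not (Overview of the medical product under investigation). The Discussion also cites an EVICEL trial in TKR that found no reduction in blood loss.

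**Working it through.** **1. The plan's own figure.** Inputs from Sample size calculation: means 25 and 37 g/l, so a difference of 12 g/l; planning SD 15 g/l; two-sided 5% level; 90% power; equal groups. The exact two-sample t-test (noncentral t, 2n − 2 degrees of freedom, noncentrality 12 / (15 × √(2/n))) gives 89.3% power at n = 33 and 90.15% at n = 34. The stated 34 per group reproduces, and no covariate enters it. With the SDs quoted from the cited study, the pooled SD is √((10² + 12²)/2) = 11.05 g/l, and 34 per group gives about 99% power. The SD of 15 g/l therefore already holds a reserve.

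**2. Does the Hb fall depend on blood volume?** Assumed, not in the documents: simple dilution, baseline Hb 140 g/l, loss 1.2 l. Fall = 140 × (1 − exp(−1.2/volume)), which gives 36.3, 29.9 and 25.4 g/l at 4, 5 and 6 l. The slope is (36.3 − 25.4)/2 ≈ 5.5 g/l per litre.

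**3. What this means between arms.** With an assumed blood volume SD of 0.8 l, the standard error of the difference in mean volume between arms is 0.8 × √(2/34) = 0.19 l. A one-standard-error imbalance moves the treatment estimate by 0.19 × 5.5 ≈ 1.1 g/l. The planned standard error of the treatment difference is 15 × √(2/34) = 3.6 g/l.

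**4. How much residual variance could be explained?** Simulation, all inputs assumed: 60% women; BMI up to 35; blood volume from a formula in sex, height and weight (mean 4.8 l, SD 0.8 l); lognormal loss with median 1.2 l and log-SD 0.3, 0.4 or 0.5; dilution as above; 5 g/l of measurement noise. Reduction in residual variance when blood volume is added to baseline Hb:

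| Blood loss in relation to blood volume | Reduction |
|---|---|
| Unrelated | 7 to 16% |
| Rises with its square root | 2 to 5% |
| Fully proportional | 0% |

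**5. Effect on power and interval width.** Residual SD = 15 × √(1 − R²), where R² is the assumed extra variance explained and 15 g/l is taken as the residual SD with baseline Hb alone. With 34 per arm and two covariates there are 64 degrees of freedom. Half-width = t(0.975; 64) × residual SD × √(2/34).

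| Extra R² | Residual SD (g/l) | Power at 12 g/l | Power at 9 g/l | 95% CI half-width (g/l) |
|---|---|---|---|---|
| 0% | 15.0 | 90.1% | 68.3% | 7.3 |
| 5% | 14.6 | 91.5% | 70.5% | 7.1 |
| 10% | 14.2 | 92.8% | 72.9% | 6.9 |
| 15% | 13.8 | 94.1% | 75.3% | 6.7 |

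The 9 g/l column is an illustration of a smaller true effect, not a figure from the protocol.

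**6. Cost if blood volume explains nothing.** At R² = 0, power is 90.14% with baseline Hb alone, 90.12% with one further covariate and 90.10% with three further covariates (sex, height and weight separately).

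**The case against.** The strongest reply is that nothing here is wrong. ANCOVA on the baseline value is a sound primary analysis. Under randomisation, omitting a prognostic covariate neither biases the treatment difference nor inflates the type I error, and the confidence interval already allows for chance imbalance. The documents contain no figure showing that the gain exceeds zero, and they give no blood-volume formula. All of this stands. It limits the point to precision. The lack of a formula is no obstacle, since sex, height and weight can enter directly.

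The full protocol or SAP might be expected to settle covariates. Here, however, the article itself names the model and its covariate, so the choice can be commented on.

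Three stronger readings may tempt a reader, and the documents do not support them:

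- **That the sample size relies on covariates the model then omits.** The 34 per group follows from an unadjusted t-test, and the covariate named as the example, baseline Hb, is the one used. There is no contradiction.
- **That the Hb minimum ignores transfusion.** Subject withdrawal sets rules: no randomisation after an earlier intraoperative transfusion, the largest control-group difference for transfusion during surgery after randomisation, an Hb measurement before postoperative transfusion, and the smallest observed Hb where a patient deteriorates despite it. Only the number of units, recorded under Postoperative procedure ("number of units transfused, date of transfusion, Hb value before transfusion"), is not used in the Hb endpoint.
- **That body size can shift Hb fall by about as much as the planning effect.** The gap of 11 g/l between 4 l and 6 l of blood volume contrasts two individuals, whereas 12 g/l is a difference between group means. The like-for-like figure is the 1.1 g/l in step 3.

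**Conclusion.** The point holds as a minor, optional improvement in precision. The primary ANCOVA is valid as written and the sample size is correct on its own inputs. Adjusting for baseline Hb alone may leave explainable variation between patients in the error term. At the planning values the gain from adding blood volume is between 0 and about 4 percentage points of power, and at best about 0.6 g/l off the half-width of the confidence interval. This rests on an assumed extra R² of 0 to 15%, a range supported only by dilution arithmetic and simulation on assumed inputs. Where the truth lies depends on how blood loss scales with blood volume, which the documents do not tell. The suggestion is worth making because it costs practically nothing and recruitment has not begun.

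**What to change.** Before recruitment, amend Statistical methods so that the primary ANCOVA has baseline Hb and estimated blood volume as prespecified covariates. Name the blood-volume formula, or enter sex, height and weight directly. All of these are recorded before randomisation. Factors recorded after randomisation, such as units transfused, should not be added as covariates.

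The cost is a sentence in the plan, a few lines of code and one degree of freedom (three if sex, height and weight enter separately), which is less than 0.1 percentage point of power. No new data are needed, and the sample size stays as it is.

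Optionally, add one supportive analysis of calculated total blood loss in ml, from estimated blood volume, the Hb fall and the units transfused. It would express the result in the terms in which the endpoint is named. The primary analysis does not depend on it.

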### Risks

The following potential risks may occur when administering fibrin sealants:Immunogenicity, hypersensitivity, allergic reaction and anaphylaxis, and the possible development of antibodies against components of fibrin sealants. The risk is markedly increased when fibrin sealants are used repeatedly or in patients with a known hypersensitivity to the active substances or to any of the excipients.Thromboembolic events due to accidental intravascular administration.Transmission of infections. Standard measures to prevent infections resulting from the use of medicinal products prepared from human blood or plasma include the selection of donors, screening of individual donations and plasma pools for specific markers of infection, and the inclusion of effective manufacturing steps for the inactivation/removal of viruses. The measures taken are considered effective for enveloped viruses such as HIV, hepatitis C virus and hepatitis B virus, and for the non-enveloped hepatitis A virus. The measures taken may be of limited value against non-enveloped viruses such as parvovirus B19.Complications related to infections or thromboembolism, postoperative wound complications.Tissue adhesion at undesired sites owing to incorrect product application.

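### The only method stated for AEs and SAEs is a chi-squared test with no estimate or interval, and the P <0.05 rule is not restricted to exclude it

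*Protocol article*

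**What the plan says.** The Statistical methods section of the protocol article has one sentence on safety analysis: "AEs and SAEs will be evaluated descriptively by chi-squared tests". Later in that section, with no restriction to particular endpoints, it says: "The *P* values will be assessed descriptively and will be deemed significant when *P* <0.05".

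The section treats other outcomes differently. The primary endpoint is decided on a 95 % CI for the difference in means, and the need for transfusion is given an odds ratio with a 95 % CI.

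The Risks section lists harms of fibrin sealants without rates: hypersensitivity and allergic reactions, thromboembolic events, transmission of infection, tissue adhesion at unwanted sites, and "Complications related to infections or thromboembolism, postoperative wound complications".

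The trial size comes from haemoglobin alone: "With a power of 90 % and an estimated SD of 15 g/l, the required number of cases is 34 per group".

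**The concern.** The safety sentence pulls in two directions. A descriptive evaluation would consist of counts, percentages and differences. A chi-squared test is a significance test, and the P value it produces falls under a rule that labels results significant or not.

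With 34 patients per arm, that label carries little information about an uncommon complication. A report that followed the sentence literally could give one P value per comparison and leave the reader unable to see how large an excess of harm the data still allow. The product is made from human plasma and has named thromboembolic and infective risks, so that is the figure a reader would want. The plan already asks for an interval for transfusion, and asking for one here would be consistent.

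**Working it through.** **1. The plan's own sample size.** Inputs from Sample size calculation: difference 37 - 25 = 12 g/l, SD 15 g/l, two-sided alpha 0.05, power 90 %. The normal approximation is n = 2(1.960 + 1.282)² × 15² / 12² = 32.8, so 33 per arm. The exact t-test has power 89.3 % at 33 and 90.2 % at 34. The stated 34 per arm reproduces. It says nothing about harms, and it was not meant to.

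**2. Chance that a real rise in an event is non-significant.** The document gives no event rates, so the rates below are assumptions. All 35 × 35 possible tables for two independent Binomial(34, p) arms were enumerated. The miss rate is 1 minus the probability of P <0.05 with the uncorrected Pearson test.

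| Assumed control rate | Threefold rise missed | Fourfold rise missed |
|---|---|---|
| 1 % | 99 % | 97 % |
| 2 % | 92 % | 84 % |
| 3 % | 84 % | 70 % |
| 5 % | 70 % | 49 % |
| 10 % | 44 % | 15 % |

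The result depends strongly on the base rate. At 3 % or less most such rises are missed. At 5 % a fourfold rise is about even, and at 10 % a fourfold rise is usually detected.

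**3. What the test shows and what an interval shows.** Take 1 event in 34 on control and 4 in 34 on EVICEL.

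- Pearson: 68 × (1×30 - 4×33)² / (34 × 34 × 5 × 63) = 1.94, so P = 0.16.
- Risk difference: 4/34 - 1/34 = 8.8 points.
- Wilson 95 % limits: 4.7 to 26.6 % for 4/34, and 0.5 to 14.9 % for 1/34.
- Newcombe lower limit: 8.8 - √[(11.8 - 4.7)² + (14.9 - 2.9)²] = -5.1 points.
- Newcombe upper limit: 8.8 + √[(26.6 - 11.8)² + (2.9 - 0.5)²] = +23.9 points.

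The P value reports no significant difference. The interval shows that an excess of up to about 24 points has not been excluded.

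**4. No events in either arm.** The chi-squared statistic is undefined. The Wilson upper limit for 0/34 is 10.2 %, so the Newcombe interval for the difference runs from -10.2 to +10.2 points. The data still bound the risk, although no P value exists.

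**5. Sparse counts.** With fewer than 10 events in total, the expected number of events is below 5 in each arm. With 0 versus 4 events, Pearson gives P = 0.039 and Fisher's exact test gives P = 0.114, so the label depends on the version of the test.

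**The case against.** The text labels both the safety evaluation and the P values descriptive, and the trial objectives include no safety hypothesis. A reader might infer that harm is to be judged by significance alone and that a non-significant result would count as evidence of safety. The documents do not support this: no sentence ties a safety conclusion to the test. That part of the objection stands in full.

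Low power for uncommon harms is general to trials sized on an efficacy endpoint and is not an error in this plan. That also stands. Reporting an interval would not raise the power.

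All event rates above are assumed, and the article does not say whether each named risk will be tested separately. Counts of any AE over 12 months could be much larger, and there the sparse-count difficulty may not arise. This limits the point to uncommon event types.

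Other planned comparisons bear on harm, such as the log-rank test of time until wound healing. The claim here is therefore only that chi-squared is the sole method stated for AEs and SAEs.

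Finally, this is a condensed article, and a full analysis plan may add per-arm counts and intervals. Their absence alone would be no finding. But the article does more than stay silent. It names a method and a threshold, and a better method costs almost nothing.

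**Conclusion.** The point holds as a minor one. The article fixes a chi-squared test for AEs and SAEs and leaves it under a rule by which results "will be deemed significant when *P* <0.05", with no estimate alongside. At 34 per arm this tells a reader little about uncommon harms. Under assumed control rates of about 3 % or less, a three- to fourfold rise is non-significant in about 70 % or more of trials. At 5 to 10 % the range is about 15 % to 70 %. These figures rest on the uncorrected Pearson test, complete data on 34 per arm, and rates that the document does not supply.

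A reader might go further and say that a several-fold rise would usually be missed whatever the event. The figures do not bear that out: at 10 % versus 30 % the miss rate is about 44 %, and at 10 % versus 40 % about 15 %. The primary and secondary efficacy conclusions are not affected.

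**What to change.** In Statistical methods, replace the AE sentence with:

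> For any AE, any SAE and each risk named under Risks, the number and percentage of patients with at least one event will be given per arm, with the risk difference (EVICEL minus control) and its 95 % Newcombe CI.

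Then restrict the P <0.05 sentence so that it does not apply to AEs and SAEs.

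Switching to Fisher's exact test is not part of this fix. It would raise the miss rate (from 84 % to 97 % at 3 % versus 9 %), while the Pearson test's actual type I error stays at or below about 6 % at the rates checked (1 to 10 %).

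The cost is two sentences and a few lines of analysis code, with no extra patients, data or visits. Trial status says that recruitment has not started, so the change can be made before any data exist. The small downside is that the wide intervals will show how little 68 patients can say about uncommon harms.
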